# CApecitabine plus Radium-223 (Xofigo™) in breast cancer patients with BONe metastases (CARBON): study protocol for a phase IB/IIA randomised controlled trial

**DOI:** 10.1186/s13063-019-3643-6

**Published:** 2020-01-15

**Keywords:** Radium-223, Capecitabine, Bone metastases, Bone turnover markers, Breast cancer

## Abstract

**Background:**

A substantial proportion of breast cancer patients develop metastatic disease, with over 450,000 deaths globally per year. Bone is the most common first site of metastatic disease accounting for 40% of all first recurrence and 70% of patients with advanced disease develop skeletal involvement.

Treatment of bone metastases currently focusses on symptom relief and prevention and treatment of skeletal complications. However, there remains a need for further treatment options for patients with bone metastases. Combining systemic therapy with a bone-targeted agent, such as radium-223, may provide an effective treatment with minimal additional side effects.

**Methods/design:**

CARBON is a UK-based, open-label, multi-centre study which comprises an initial safety phase to establish the feasibility and safety of combining radium-223 given on a 6-weekly schedule in combination with orally administered capecitabine followed by a randomised extension phase to further characterise the safety profile and provide preliminary estimation of efficacy.

**Discussion:**

The CARBON study is important as the results will be the first to assess radium-223 with chemotherapy in advanced breast cancer. If the results find acceptable rates of toxicity with a decrease in bone turnover markers, further work will be necessary in a phase II/III setting to assess the efficacy and clinical benefit.

**Trial registration:**

ISRCTN, ISRCTN92755158, Registered on 17 February 2016.

**Electronic supplementary material:**

The online version of this article (10.1186/s13063-019-3643-6) contains supplementary material, which is available to authorized users.

## Background

### Metastatic breast cancer

Despite significant advances and improvements in outcomes following breast cancer, a significant proportion of patients still develop metastatic disease with bone being the most common first site for distant metastasis. Metastatic tumour development is thought to follow complex interactions between the tumour cell and the bone microenvironment allowing occupation of the haematopoietic stem cell and other cellular niches in the bone marrow by tumour cells. Tumour-derived factors attract and stimulate osteoclasts, increasing bone turnover and releasing bone-activated growth factors and cytokines [1]

The skeletal lesions seen in association with breast cancer are most commonly osteolytic and associated with significant morbidity due to the skeletal complications, termed skeletal-related events (SREs): severe bone pain requiring radiation, pathological fracture, spinal cord or nerve root compression, hypercalcaemia and the requirement of surgery or radiation to bone. However, there is usually an osteoblastic component that is manifested by the visualisation of bone metastases on radionuclide bone scans and elevation of osteoblastic bone markers such as bone-specific alkaline phosphatase (B-ALP). Although sometimes identified on imaging tests, most SREs are associated with symptoms when they are known as symptomatic skeletal events (SSEs). The median survival time after the development of bone metastases is approximately 2–3 years.

Bone turnover markers, biological indicators of either bone resorption or bone formation, are associated with clinically relevant endpoints. *N*-telopeptide of type-I collagen (NTX) is derived from the breakdown of type-1 collagen during bone remodelling and reflects the rate of bone resorption. Elevated levels of urinary NTX (uNTX) are associated with significantly increased rate of SREs and disease progression amongst a solid tumour population, in addition to increased mortality. B-ALP is a bone-formation marker which is similarly associated with negative outcomes in patients with elevated levels [2].

There are many treatment options available to patients with advanced breast cancer including surgery, radiotherapy and systemic therapies. Current treatment of bone metastases also focusses on symptom relief and treatment and prevention of SREs. Anti-resorptive agents, such as bisphosphonates or denosumab, delay SREs and are subsequently now widely established as standard therapy for such patients [3–6]. Additionally, bisphosphonates suppress bone turnover markers, with their normalisation or degree of suppression correlating with reduced SREs and death rate [7]. However, there remains a need for further treatment options for patients with bone metastases to improve survival more than 2–3 years. Combining systemic therapy with a bone-targeted agent, such as radium-223, may provide an effective treatment with minimal additional side effects.

### Radium-223

Radium-223 dichloride (radium-223) is a novel alpha-emitting pharmaceutical that has been developed for the treatment of bone metastases. The product is based on the alpha-emitting radionuclide radium-223. The intrinsic bone-targeting property of radium-223 compounds is similar to that of other alkaline earth elements, like calcium. The characteristics of alpha-emitting radionuclides have benefits over beta-emitting radionuclides for bone targeting. Firstly, radium-223 emits alpha-particles with high linear-energy transfer and a radiation range limited to less than 100 μm [8–11]. This generates a highly localised and effective radiation zone with high probability of inducing double-strand DNA breaks in the cancer cells. LOn the other hand, beta-emitting radiopharmaceuticals, such as strontium, emit particles with lower energy, mainly inducing single-strand breaks which are more easily repaired. Additionally, beta-particles typically have 30–80 times longer radiation range compared to alpha-particles. An alpha-emitting radiation source located in a target tissue, such as bone metastases, will deliver higher energy radiation to a more localised volume than beta emitters, thereby reducing exposure of surrounding normal tissues and leading to less toxicity, importantly less myelotoxicity. Radium-223 received Food and Drug Administration (FDA) approval in 2013 for the treatment of patients with castration-resistant prostate cancer (CRPC) and bone metastases [12].

### Pre-clinical data

Pre-clinical data in an experimental skeletal metastasis model in nude rats inoculated intravenously with human breast cancer cells demonstrated a significant radium-223 anti-tumour effect and showed significantly symptom-free survival [13].

### Clinical data

Since radium-223 began clinical development in 2001 there have been several phase I studies in patients with bone metastases from prostate or breast cancer. These showed that the drug is quickly eliminated from blood, taken up by bone and excreted via the small intestine [13]. The kidneys, bladder and urethra are, therefore, exposed to minimal amounts of radiation. No specific uptakes were seen in the heart, liver, kidney, gallbladder, stomach or spleen. The highest absorbed doses were measured in the bone and red marrow.

Pain relief was observed in studies using both single doses and multiple doses of radium-223, with better pain relief being observed with the higher doses [14, 15]. Decreases in B-ALP were observed at all dose levels, similarly more pronounced at the higher doses [14].

Multiple dosing at 6-weekly intervals was evaluated in the BC1–04 study, a phase II study in patients with symptomatic or non-symptomatic hormone-refractory prostate cancer. One hundred and twenty-two patients received three doses of 25, 50 or 80 kBq/kg. A significant dose-response relationship was seen, with an increasing proportion of prostate-specific antigen (PSA) responders and B-ALP responders with increasing dose. The two highest dose levels had a greater effect than the lowest dose levels, with no significant difference between 50 and 80 kBq/kg [16].

### Prostate cancer – single agent and combination with chemotherapy

The majority of studies to date have been in prostate cancer using radium-223 as a single agent. In a placebo-controlled, phase II study in hormone-refractory prostate cancer patients with bone metastases, patients were assigned 4 × 50-kBq/kg radium-223 injections (*n* = 33) or saline injections (*n* = 31) given every 4 weeks [17]. The median relative change in B-ALP was significantly greater in the treatment arm compared with the control arm (− 65.6% vs. 9.3%; *P* < 0.0001). Toxicity from radium-223 is mild and tolerable. The most common Adverse Events (AEs) were reversible myelosuppression, diarrhoea, nausea and vomiting, with all reported as mild or moderate in severity. A combined analysis of 300 patients treated with radium-223 showed that radium-223 is well tolerated with a low propensity for haematological toxicity [18].

The phase III registration study of radium-223 (ALSYMPCA) was performed in 921 patients with CRPC and bone metastases and compared best supportive care with radium 50 kBq/kg every 4 weeks for six cycles or placebo. The primary endpoint was overall survival. Patients who received radium-223 had a significant 3.6-month improvement in median survival (hazard ratio (HR) = 0.70; 95% confidence interval (CI), 0.58–0.83; *P* = 0.001) compared with patients who received placebo [12]. These benefits were achieved without significant toxicity and with additional benefits on the frequency of SSEs, even in the presence of concomitant bisphosphonates [19].

### Rationale for using radium-223 to treat metastatic breast cancer

The mechanism of action and efficacy of radium-223 in prostate cancer suggests that the agent may be effective in other cancers that have a propensity to metastasise to the bone. This was confirmed in an open-label, phase IIa, non-randomised study of radium-223 in breast cancer patients with bone-dominant disease. This study evaluated any clinically relevant effect on bone markers in breast cancer patients who had progressed on endocrine treatment and were no longer considered suitable for further endocrine therapy.

Radium-223 significantly reduced uNTX and B-ALP from baseline to end of treatment. Radium-223 was safe and well tolerated [16]. Therefore, it is important to assess the toxicity and efficacy of radium-223 in a population of patients that commonly requires chemotherapy. Currently, larger randomised trials are evaluating the addition of radium-223 to an aromatase inhibitor alone or with everolimus (ClinicalTrials.gov Identifiers: NCT02258451 and NCT02258464). The results are anticipated in 2020. Combinations with chemotherapy are also of interest for treatment later in the clinical course. Capecitabine was selected due to its frequent use as a single agent in breast cancer and relative lack of myelotoxicity. The combination may, therefore, target both bone metastases and visceral metastases.

There are ongoing studies combining radium-223 with endocrine treatments (NCT02258464 and NCT02258451) and a small safety study (n=15) has evaluated the combination of paclitaxel and radium-223 in a mixed population of cancer patients [1], but thisThis will be the first study to specifically assess radium with chemotherapy in advanced breast cancer.

## Methods/design

### Study aims and objectives

The purpose of this study is to determine the safety profile and clinical relevance of the combination of radium-223 and capecitabine in breast cancer patients with bone metastases. The study protocol and this manuscript have been written in accordance with Standard Protocol Items: Recommendations for Interventional Trials (SPIRIT) guidelines.

#### Primary objectives

To evaluate the safety and toxicity of the combination of radium-223 and capecitabineTo preliminarily estimate if multiple intravenous (i.v.) injections of radium-223 plus capecitabine will have any clinically relevant effect on uNTX in breast cancer patients with bone metastases, with or without other sites of disease

The sample size calculation is based solely on the primary toxicity endpoint. Primary analysis of the uNTX endpoint is focussed on estimation only, i.e. no formal hypothesis testing will be carried out for the purpose of decision making. No formal comparisons will be made.

#### Secondary objectives

To evaluate the effect of radium-223 on other bone turnover markers (*N*-terminal propeptide of procollagen type-1 (P1NP), serum C-telopeptide (CTX), pyridinoline cross-linked carboxyterminal telopeptide (1CTP), B-ALP)
To evaluate pain scores and quality of lifeTo evaluate time to first SSE – defined as any of: use of external-beam radiotherapy to relieve skeletal symptoms; new symptomatic pathological vertebral or non-vertebral bone fracture; spinal cord compression; tumour-related orthopaedic surgical interventionTo evaluate time to progression of bone disease and time to progression of extraskeletal disease

### Study design

The trial is designed as a randomised, controlled, open-label, multi-centre, phase IB/IIA study. It comprises an initial safety phase to establish the feasibility and safety of combining radium-223 at the recommended dose of 55 kBq/kg given on a 6-weekly schedule to enable combination with orally administered capecitabine administered with the standard of care schedule (2 weeks of capecitabine followed by 1 week off treatment). Recruitment to the initial safety phase utilises a 3 + 3 design. If the treatment in the initial safety phase proves to be feasible and safe, the randomised extension phase will open to recruitment. The extension phase of the study aims to characterise the safety profile and provide preliminary estimation of efficacy.

The participant pathway can be seen schematically in Fig. 1 and a populated Standard Protocol Items: Recommendations Figure is also provided in Fig. 2.

**Fig. 1 Fig1:**
[figure not shown]
Participant pathway

**Fig. 2 Fig2:**
[figure not shown]
Standard Protocol Items: Recommendations for Interventional Trials (SPIRIT) Figure. Schedule of enrolment, interventions and assessments for participants who are suitable for enrolment to the trial

### Study population

Patients are eligible if they have histological evidence of primary breast cancer with imaging evidence of bone metastases (with or without soft tissue, lymph node or visceral metastases; brain metastases allowed if stable and untreated for ≥ 8 weeks) and systemic chemotherapy with capecitabine is felt to be appropriate by the treating physician. They must have received no more than two lines of chemotherapy in the metastatic setting and prior cytotoxic therapy must have been completed 28 days or more prior to initiation of study treatment. They must have an Eastern Co-operative Oncology Group (ECOG) performance status 0–2 and a life expectancy of 6 or more months. Patients are required to have appropriate haematological and biochemical parameters, to be aged 18 years or over and be able and willing to consent and comply with study treatment, visits and required investigations.

Patients are excluded from the study if they are pregnant or breast feeding; received an investigational drug within 4 weeks prior to the first study treatment; received external-beam radiotherapy within 4 weeks prior to the first study treatment; they have the presence of imminent or established spinal cord compression based on clinical findings and/or magnetic resonance imaging (MRI); presence of other currently active (diagnosis within the last 5 years) malignancy (except treated non-melanoma skin cancer (basal or squamous), carcinoma in situ of the cervix and superficial bladder cancers). Patients are also excluded if they have had severe and unexpected reactions to fluoropyrimidine therapy or have been diagnosed with dihydropyrimidine dehydrogenase deficiency; received a blood transfusion or erythropoietin within 4 weeks of study treatment; are hypersensitive to capecitabine or any of its excipients; have received treatment with sorivudine or its chemically related analogues, such as brivudine; and are receiving treatment with phenytoin or warfarin. Patients with any other serious illness or medical condition will be excluded, such as, but not limited to: any uncontrolled infection, clinical heart failure (NYHA Heart Failure Class III or IV), active Crohn’s disease or ulcerative colitis, bone marrow myelodysplasia, uncontrolled coronary artery disease, active peptic ulcers, malabsorption.

### Sample size

Approximately 48 participants will be recruited across both phases of the trial.

#### Initial safety phase

A minimum of six and a maximum of 12 evaluable participants will be recruited into the initial safety phase. This is based on the number of participants experiencing Dose Limiting Toxicities (DLTs), using a modified 3 + 3 approach (see Fig. 3).

**Fig. 3 Fig3:**
[figure not shown]
Dose Limiting Toxicity (DLT) schema

#### Extension phase

An additional 36 participants will be recruited to the extension phase, and will be randomised on a 1:2 ratio to receive either:
Orally administered capecitabine alone 1000 mg/m^2^ twice a day (bd) or, capecitabine 850 or 1000 mg/m^2^ bd (as determined in the initial safety phase) plus radium-223 55 kBq/kg by i.v. injection on day 1 of cycle (2, 4, 6, 8, 10 and 12) of capecitabine for a total of six injections.

The sample size for the extension phase is based upon the primary toxicity endpoint of grade-III/IV toxicity. With 24 participants in the capecitabine plus radium-223 arm, this provides approximately 80% power to exclude a grade-III/IV diarrhoea rate of 25% from the upper limit of a one-sided 85% CI, assuming a rate of approximately 10% with capecitabine alone. If no more than 3/24 participants experience grade-III/IV diarrhoea the upper limit of the one-sided 85% CI will exclude 25%.

The control arm is included to provide concurrent standard of care data for interpretation only. No formal comparisons between arms will be made.

### Recruitment

Participants are recruited from NHS hospitals throughout the UK which are approved to participate in this study having obtained requisite ethical and management approval. There are four centres open to recruitment; Weston Park Hospital in Sheffield, St James’s Hospital in Leeds, The Christie Hospital in Manchester and the Clatterbridge Cancer Centre in Liverpool. These centres have been selected based on their proven track record in delivering early phase studies and experience with radium-223. Further centres may be considered if the recruitment target is not being met. The estimated accrual for this study is two to three participants a month. Thus, participant accrual is expected to be completed within 18 months.

### Study treatment

A maximum of 12 cycles of combination therapy is given unless disease progression or unacceptable toxicity are encountered. A cycle is 21 days in accordance with the standard administration of capecitabine.

A maximum of two doses of capecitabine are being investigated in this study; 850 mg/m^2^ bd and 1000 mg/m^2^ bd. The starting dose is 1000 mg/m^2^ bd which is in accordance with the standard administration of capecitabine. Capecitabine is delivered on days 4–17 for up to 12 cycles to provide a 3–4-day window before and after radium-223 to minimise any risk of potentiating normal tissue radiation sensitivity. After cycle 12, patients may continue with capecitabine off study as per standard of care, if they are continuing to receive clinical benefit.

Radium-223 is administered at 55 kBq/kg. This dose has been selected based on clinical data from previous studies in prostate cancer and breast cancer which have demonstrated efficacy and tolerability [14, 16–18]. Radium-223 is administered as a slow i.v. injection on day 1 of alternating cycles, starting at cycle 2 to provide one cycle of safety information in each participant with capecitabine alone.

#### Initial safety phase

The safety data for the first cohort is reviewed by the Safety Review Committee and the capecitabine dose will either be expanded to a further three participants or de-escalated to 850 mg/m^2^ bd depending on the frequency and severity of toxicity experienced.

Toxicity data for each subsequent cohort is reviewed prior to dose expansion after three participants have been recruited and observed for DLTs, according to Fig. 3.

DLTs are assessed during the second cycle of capecitabine treatment up to the administration of cycle 3 day 1 and will be defined as the following events:
Gastrointestinal toxicity of ≥ grade III lasting > 48 h despite adequate supportive care measuresHaematological toxicity ≥ grade IV lasting > 7 days despite adequate supportive care measures which should exclude the use of bone marrow growth factors

Gastrointestinal toxicity ≥ grade III or haematological toxicity≥ grade IV experienced by participants during the first cycle, i.e. up to the administration of cycle 2 day 1 are not classed as DLTs as they are related to the capecitabine only.

The number of participants recruited to the initial safety phase, and the dose carried forward to the randomised extension phase is determined by the number of DLTs in line with the DLT schema.

#### Evaluability

Participants can miss no more than 50% of doses in the first two treatment cycles in order to be evaluable for DLT in the initial safety phase. Participants missing more than 50% of doses for reasons other than toxicity without experiencing a DLT will be replaced.

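### DLT evaluability is counted over cycles 1 and 2 together and does not require radium-223, so participants without the combination in cycle 2 can count as evaluable and DLT-free

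*Protocol article*

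**What the plan says.** All references are to the protocol article.

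- **Evaluability** (under Study treatment) sets the threshold: "Participants can miss no more than 50% of doses in the first two treatment cycles in order to be evaluable for DLT". Replacement follows from it: "Participants missing more than 50% of doses for reasons other than toxicity without experiencing a DLT will be replaced".
- **Study treatment** gives radium-223 on day 1 of alternating cycles, "starting at cycle 2 to provide one cycle of safety information in each participant with capecitabine alone". On capecitabine it says "Capecitabine is delivered on days 4–17 for up to 12 cycles", and the dose is taken twice a day.
- **Initial safety phase** (under Study treatment) sets the observation window: "DLTs are assessed during the second cycle of capecitabine treatment up to the administration of cycle 3 day 1". Severe events in cycle 1 "are not classed as DLTs as they are related to the capecitabine only". The same section lets the number of DLTs determine the size of the phase and the dose taken into the randomised extension.
- **Initial safety phase** (under Sample size) counts the phase in evaluable participants: "A minimum of six and a maximum of 12 evaluable participants will be recruited into the initial safety phase".
- **Statistical analysis** defines the safety-phase analysis population on another basis, namely receipt of at least one complete cycle of capecitabine and radium-223.

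**The concern.** A 3 + 3 decision treats each evaluable participant without a DLT as evidence that the combination was tolerated. That holds only if the participant received the combination during the window in which a DLT could be recorded.

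The stated rule does not secure this, for two separate reasons. First, half of the capecitabine doses in its base belong to cycle 1, where no event can be a DLT, so a full cycle 1 can offset an empty cycle 2. Second, the single radium-223 injection is either not counted as a dose or is one dose among 57, so missing it hardly moves the percentage.

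A participant who passes the threshold falls outside the replacement sentence. With cohorts of three, one such participant is a third of the evidence at that step. If that participant's DLT risk is below that of the combination, the error runs in one direction, towards accepting the dose.

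**Working it through.** The 50% threshold has no derived figure behind it in the article, so there is none to reproduce. The check applies the rule to its own dose base.

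**Dose base** (Study treatment)
- Capecitabine days per cycle: 17 − 4 + 1 = 14.
- Capecitabine doses per cycle: 14 × 2 = 28. Over two cycles: 56.
- Radium-223 injections in cycles 1 and 2: one. The base is 57 if the injection counts as a dose. The article does not define a dose, so both bases are shown.

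**The rule applied, with cycle 1 taken in full**

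| Cycle 2 treatment | Missed, base 56 | Missed, base 57 | Passes? |
|---|---|---|---|
| All capecitabine, no radium-223 | 0/56 = 0% | 1/57 = 1.8% | Yes on both |
| Radium-223, no capecitabine | 28/56 = 50.0% | 28/57 = 49.1% | Yes on both (exactly 50% is allowed) |
| No radium-223, one capecitabine dose | 27/56 = 48.2% | 28/57 = 49.1% | Yes on both |
| Neither agent | 28/56 = 50.0% | 29/57 = 50.9% | Yes on base 56 only |

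**Which feature causes which failure.** On a cycle 2 base (28 doses, or 29 with the injection), the participant with radium-223 but no capecitabine has missed 28/28 = 100% or 28/29 = 96.6% and fails. The participant with all capecitabine but no radium-223 has missed 0/28 = 0% or 1/29 = 3.4% and still passes. Pooling the cycles explains the first case. The second arises because the injection is not a condition.

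**Effect on the decision (illustration).** Assumptions: the dose is accepted with at most 1 DLT in 6, because Fig. 3 is not shown; the true DLT rate p on the combination is 33%; k of the 6 participants are under-exposed, each with DLT risk q. With m = 6 − k, let P0 = (1 − p)^m and A = P0 + m·p·(1 − p)^(m−1).

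- k = 0: A = 0.67^6 + 6 × 0.33 × 0.67^5 = 0.090 + 0.267 = 0.358.
- k = 1, q = 0: A = 0.67^5 + 5 × 0.33 × 0.67^4 = 0.135 + 0.332 = 0.468.
- k = 1, q = 0.10: 0.9 × 0.468 + 0.1 × 0.135 = 0.434.
- k = 2, q = 0: A = 0.67^4 + 4 × 0.33 × 0.67^3 = 0.202 + 0.397 = 0.599.
- k = 2, q = 0.10: 0.81 × 0.599 + 0.18 × 0.202 = 0.521.

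With q = 0 and other true rates, acceptance for k = 0, 1 and 2 is 42.0%, 52.8% and 65.2% at p = 30%, and 23.3%, 33.7% and 47.5% at p = 40%.

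**The two definitions side by side.** Evaluability asks for no more than half of the doses missed over two cycles. Statistical analysis asks for one complete cycle of capecitabine and radium-223. On a natural reading the second excludes the first two cases in the table. It could also be read as any complete capecitabine cycle, possibly cycle 1, plus radium-223, which would admit the second case. Read strictly, it could drop a participant whose DLT interrupted cycle 2.

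**The case against.** The strongest reply is that the Statistical analysis section already limits the safety-phase population to participants who received both agents. A reader might infer from the Evaluability section that the trial does count unexposed participants as DLT-free. The article does not say that. Its wording permits it, while another section points the other way. What remains is that the analysis population is not stated to govern evaluability, replacement or the cohort decision, so the conflict is open.

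Second, the Safety Review Committee reviews safety data for each cohort, and the statistician's summary after every three participants includes treatment compliance. A missed injection would probably be seen. This makes an unnoticed error less likely but does not repair the rule that the committee is given.

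Third, the acceptance probabilities rest on an assumed decision rule and an assumed DLT rate. Zero risk is also too extreme for someone who received one of the two agents in cycle 2. That is fair, and it is why a range is given.

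Fourth, the article condenses a full protocol that may define doses and evaluability more closely. That could settle the base of 56 or 57, but the first three cases in the table pass on either. The extension phase also measures grade III/IV toxicity in 24 combination participants, and its sample size is unaffected.

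A smaller point is wording. A participant who misses more than half of the doses because of toxicity, without a DLT, is not evaluable under the first sentence and not replaced under the second. The likely intention is to keep such participants, so this needs clarifying but adds little weight.

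**Conclusion.** The point holds in this form: the stated evaluability rule does not match the stated DLT window, and it conflicts with the safety-phase analysis population. Participants with a full cycle 1 but no radium-223, or no cycle 2 capecitabine, can count as evaluable and DLT-free and would not be replaced. This rests only on the article's own schedule and dose counts.

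The bias is towards accepting the dose, provided that under-exposed participants have a lower DLT risk than those on the combination. Its size is illustrative: from 36% acceptance to about 43–47% with one under-exposed participant in six and 52–60% with two, where the lower end takes their risk as 10% and the upper end as zero. These figures depend on the assumed 1-in-6 rule and the 33% rate. They are not an estimate for this trial, and the article gives no basis for saying how often such participants would occur. They do not show that a toxic dose would be carried forward.

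**What to change.** Define DLT evaluability on the DLT window. A participant is evaluable if any of these holds:

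1. A DLT occurred.
2. Radium-223 was received on cycle 2 day 1, together with at least 50% of the cycle 2 capecitabine doses.
3. Radium-223 was received, and cycle 2 capecitabine was then missed because of toxicity arising after the injection.

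All others are replaced and reported separately, including those who never received radium-223 because of cycle 1 toxicity. Keeping everyone who missed cycle 2 doses because of toxicity would not do, since it would retain that last group as DLT-free without any exposure to radium-223. Moving the 50% threshold to cycle 2 alone would not do either, since a participant who misses only the injection would still pass.

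Align the safety-phase population in Statistical analysis with this definition, so that a participant whose DLT interrupts cycle 2 is not excluded, and state that the definition governs the cohort decisions. The change affects who is counted, not treatment. It costs a paragraph of wording and possibly one or two more replacements in a phase of 6 to 12 evaluable participants.
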